#### Baseline assessments

At baseline, RAs will interview the participants using a standardized electronic questionnaire using Open Data Kit software [15]. RAs will receive 2 weeks training on data collection and ethical issues.

The questionnaire will assess socioeconomic characteristics including age, sex, ethnicity, religion, marital status, annual income, education, and lifestyle factors including smoking, alcohol intake, and physical activity. We will use the Global Physical Activity Questionnaire [16], and calculate the metabolic equivalent of task (MET) minutes per week. A weekly MET equivalent of 600 would represent 30 min of brisk walking five times per week or 15 min of running five times per week.

#### Twenty four hour diet recall

To measure dietary intake, we will conduct two interviewer-administered 24-h dietary recalls within a week. Each 24-h dietary recall will take approximately 25 min to complete. First, activities of the previous day will be documented to refresh the participant’s memory. Then, a dietitian will ask the participant to recall everything s/he consumed from the first meal to last meal. The time and place of each meal will be noted, followed by detailed information on each food including: specific brands, ingredients, and/or recipes. Participants will be asked to report their food portions using colorful examples of sizes or household measures such as spoon, bowl, etc. If a participant reports using their own recipe, then complete information on each individual ingredient will be inquired about. Energy and nutrient intakes will be calculated using the food composition table for Nepal [17].

#### Anthropometry

Body weight will be measured with minimum clothing and without shoes using an Omron Model HBF-400 scale and recorded to the nearest 0.1 pounds. The weighing scale will be calibrated to zero every day. Participants’ heights will be measured, without shoes, while the participants stand against a wall. Height will be measured using a tape measure and recorded to the nearest 0.1 cm.

#### Laboratory

Blood samples will be analyzed for HbA1c, fasting glucose, low density lipoprotein (LDL) cholesterol, high density lipoprotein (LDL) cholesterol, triglycerides, and total cholesterol. All of the laboratory procedures will be carried out in the biochemistry laboratory of DH-KUH. Blood samples will be collected using evacuated blood collection tubes. Participants will be asked to fast overnight (8–14 h). We will record the time of blood draw and their most recent shift worked prior to the blood draw. The HbA1c will be measured using Boronate affinity chromatography (Axis-Shield, Norway) [18]; fasting blood glucose using Hexodinase method (Dialab, Austria) [19]; LDL and HDL using the elimination method (Dialab, Austria) [20]; triglyceride using GPO-PAP (Dialab, Austria) [21]; and total cholesterol using CHOD-PAP (Dialab, Austria) [22]. For each type of assay, the laboratory has quality control (QC) materials (using commercially available assayed and unassayed control material) from Bio-Rad Laboratories, USA. Each QC is run at least in duplicate. External QC is arranged by internationally recognized reference laboratories that distribute batches of samples of various concentrations for each assay. The laboratory performs the External Quality Assurance Scheme from unknown assayed sample from the Department of Clinical Biochemistry CMC, Vellore, India for 23 routine parameters, 5 immunological parameters and HbA1c. Additionally, 5% of the blood samples will be obtained in duplicates and sent for testing all parameters, blinded to the laboratory personnel.

#### Control period

We will have a control period of 6 months before implementing the intervention. There will not be any contact with the enrolled participants until 6 months after the study enrollment. The control period will minimize potential biases in effect estimates, including increases or decreases in a health condition with time.

### Interventions

#### Step 1: Cafeteria intervention

After 6 months of the control period, participants will receive the cafeteria intervention (Table 2). The cafeteria intervention was developed based on the findings from four focus group discussions with cafeteria users and nine in-depth interviews with cafeteria operators and managers, about strategies to promote healthy foods in the worksite. (unpublished) The four cafeterias in the hospital will improve the quality of their meals by (1) increasing the availability of fresh fruit (not fruit juice) and vegetable options, (2) avoiding sales of sugar sweetened beverages, (3) replacing whole grains with refined grains in cooking; (4) using healthy vegetable oils such as soy and sunflower; (5) minimizing the sale of fried foods; (6) trimming animal fats from meats before cooking; (7) using healthier protein sources such as chicken, beans, and nuts (8) making potable water free of cost; and (9) reducing salt in cooking. These guidelines are based on the recommendations for a healthy diet to improve cardiovascular health [23]. To facilitate these changes, a cafeteria operation team will be formed and they will be trained on procedures to implement, supervise, and monitor the worksite’s healthy changes. In addition, we will train the cafeteria staff on healthy eating, and how to modify recipes to incorporate healthy options.

**Table 2 Tab2:** Cafeteria Intervention in the Nepal pioneer worksite intervention study

Components	Activities
Strengthen management of cafeteria	• A cafeteria improvement team will be created representing hospital management, cafeteria operation, research team, finance department, hygiene monitoring, non-communicable disease prevention, nutritionist, and human resource department • We will conduct a 2-h workshop with the team on the prevention of diabetes, hypertension, and other cardiovascular diseases via healthy eating. • The team will meet monthly to monitor the intervention; discuss and find solutions for barriers to implementation
Build capacity of cafeteria staff	• We will conduct a 2-h workshop with the cafeteria staff on the prevention of diabetes, hypertension, and other cardiovascular diseases via healthy eating • We will conduct two sessions of two-hour workshops on healthy cooking practices with the cafeteria staff
Replace healthy options for unhealthy foods	• Whole grain bread instead of white bread will be used in cooking bread omelets, or fried bread • Peanut butter will be replaced for jam • White rice will be mixed with 50% brown rice in plain rice, fried rice, and rice pudding recipes • Whole wheat flour will be mixed with all-purpose flour in 1:4 ratio in dumpling recipes • Additional vegetables and lentils will be added in chowmein, thukpa, fried rice • Lentils (black beans) will be used with beaten rice instead of potato
Remove unhealthy foods from the cafeteria	• Soda drinks (Coke, Fanta, Sprite, Pepsi, Mountain Dew) will be removed • High sugar confectioneries (cake, donut, puff, cream-donut, biscuits) will be removed
Add healthy food options	• Fresh fruits in the form of whole fruit and mixed fruit salad • Flavored water free of cost • Salad (cucumber, radish, carrots) • Whole grains (oats, whole wheat bread, popcorn)
Enhance visibility of healthy foods	• Healthy food options will appear in the front page of the electronic menu • Fruits, salads and whole grains will be organized on the front desk counter
Information, Education, Communication	• A formal launch program will be organized; all the department heads of the hospital will be invited to attend • A kickoff event will be organized in each cafeteria, with a kiosk providing information on eating healthy in the cafeteria • Posters showing the healthy eating plate and whole grain consumption will be displayed on the cafeteria walls • All employees in all of the departments of the hospital will be invited to attend a 20 min session on making healthy choices in the cafeteria

#### Step 2: The behavioral intervention

After 6 months of the cafeteria intervention, half of the participants will be randomized using computer generated random numbers to receive a cafeteria and behavioral intervention (CB), the other half of the participants will continue to receive the cafeteria only (CO) intervention. The behavioral intervention will be comprised of intensive education sessions, group counseling, and goal setting and monitoring exercises based on the Diabetes Prevention Program (DPP) [24] tailored to local needs. The curriculum includes 24 sessions of 16 core weekly sessions during the first 4 months of this phase of the intervention followed by 8 weekly maintenance sessions. Each session will be 1 h long, and will be facilitated by a dietitian. Broadly, the curriculum covers subject matters of importance for achieving and maintaining healthy weight, eating a healthy diet, increasing physical activity, stress management, and overcoming common challenges encountered when making lifestyle changes. Similar to the cafeteria intervention, healthy eating messages include increasing fresh fruits and vegetable intake, avoiding added sugar, choosing whole grains, choosing healthier sources of protein, reducing sodium, and monitoring portion sizes. Participants will be encouraged to keep food and activity diaries throughout the course of the study. The maintenance period’s focus will be on overcoming declines in motivation and maintaining long-term healthy behaviors. All of the sessions will be conducted at the worksite during the workday. There will be about 20 participants in each education class. Participants will set a minimum of two lifestyle-change goals (e.g. Half of their total grain intake will be whole grains, walking 30 min a day, or reducing 7% of their body weight).

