**Methods:**

The Nepal Pioneer Worksite Intervention Study is a two-step intervention study conducted in Dhulikhel Hospital in eastern Nepal. In the first step, we will assess the effectiveness of a 6-month cafeteria intervention on cardio-metabolic risk using a pre-post design. In the second step, we will conduct a 6-month, open-masked, two-arm randomized trial by allocating half of the participants to an individual behavioral intervention based on the ‘diabetes prevention program’ for the prevention of cardio-metabolic risk. We will recruit 366 full time employees with elevated blood pressure, fasting blood sugar, or glycosylated haemoglobin (HbA1c). At baseline, we will measure their demographic variables, lifestyle factors, anthropometry, fasting blood sugar, HbA1c,and lipid profiles. We will measure cardio-metabolic outcomes at 6 months, 12 months, and 18 months.

At 12 months, we will compare the proportion of participants who have attained two or more cardio-metabolic risk factor reduction goals (HbA1_c_ decrease ≥0.5%; systolic blood pressure decrease ≥5 mmHg; or triglycerides decrease ≥10 mg/dL) during the cafeteria intervention period and the control period using generalized estimating equations. At 18 months, we will compare the proportion from the ‘cafeteria only arm’ to the ‘cafeteria and behavior arm’ for the same outcome using a chi-square test.

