#### Effectiveness of the behavioral intervention

At the 18-month follow-up, we will compare the proportion of participants who have achieved two or more of their cardio-metabolic risk factor reduction goals in CO arm to the proportion of participants in the CB arm using a *χ*^2^ test. In the event that randomization does not appear to have controlled for differences between the treatment and control groups on baseline characteristics, in secondary analysis, we will statistically control for those differences using the GEE approach with the binary distribution, logit link function and an exchangeable working correlation structure [27].

Our secondary analysis will compare the change in HbA1c, systolic blood pressure, and lipids during the cafeteria-only intervention to the change during the control period using a paired t-test. Similarly, we will compare the change in HbA1c, systolic blood pressure, and lipids between CO group and CB group using a paired t-test. Assumptions of the statistical tests will be examined and if violated non-parametric testing will be explored. In the event that randomization does not appear to have controlled for differences between the treatment and control groups in baseline characteristics, we will conduct the GEE approach with the Gaussian distribution, identity link function and an exchangeable working correlation matrix [27] to adjust for potential confounding factors. The data will be analyzed using STATA-15.

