### Sample size and power

The pre-post design, with at least 366 eligible and enrolled participants [28] and 5% loss to follow-up (LTF) after 12 months, will have over 90% of power to detect the primary effectiveness endpoint of this trial, of 31.5% or greater, compared to the 21% change in the control group seem previously in a South Asian population [29]. For the analysis of two randomized groups (CO and CB arms), with 320 participants, we will be able to detect a relative risk of 1.5 given 0.315 risk probability in the control group, 5% LTF rate with 80% power and 5% level of significance [30].

In the secondary analysis, where we will compare the within-participant changes in HbA1c, systolic and diastolic blood pressure, and lipids observed in the cafeteria intervention to those observed in the behavioral intervention. Given the sample sizes of 366 and 320 respectively, 5% LTF rate with 80% power and 5% level of significance, we will be able to detect the minimum differences as presented in Table 3. For the before-after design, we considered three possible values of the correlation (*ρ* = 0.5, 0.6, 0.7) between repeated measurements during the control period and during the intervention period.

**Table 3 Tab3:** Minimum absolute detectable differences for the change in glycosylated hemoglobin, systolic and diastolic blood pressure, and triglyceride for sample sizes of 366 and 320 correspondingly, 5% loss-to-follow-up rate with 80% power and 5% level of significance, for the Nepal Pioneer Worksite Intervention Trial

		Minimum absolute detectable difference			
		*N* = 366			*N* = 320
Parameter	Std. Dev.	*ρ*^∗^=0.5	*ρ*^∗^=0.6	*ρ*^∗^=0.7	Independent samples
Glycated hemoglobin, %	0.38	0.06	0.05	0.045	0.12
Diastolic blood pressure, mmHg	9.43	1.4	1.3	1.1	3
Systolic blood pressure, mmHg	13.32	2	1.8	1.6	4.3
Triglycerides, mg/dL	82.47	12.5	11.2	9.7	26.6

*Correlation between the changes of the same individual observed during control and treatment periods of time

Standard deviations are calculated from the baseline data of the study participants

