### Minimization of contamination

The risk and level of contamination during the randomized study phase for the behavioral intervention will be monitored at the participant level. The participants will be instructed not to share information about the study and not to provide any support to people in their worksite, other than their classmates. The behavioral classes will be conducted in a separate building outside of their workspace to ensure privacy. Further, we will measure possible contamination by asking if the participants have received any information / advice regarding diet and lifestyle changes from any of their peers and if they did, collect the name and contact information of the peer. If the contamination is found to be significant, we will make adjustments by adding the contamination as a variable in the final model while estimating the effect in secondary analysis.

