We have some limitations. First, the nurses work in shifts of 8 h in the morning, afternoon or night. Their biological measures might be influenced by their shifts of the previous day. Second, we anticipate that their participation in the individual behavior component will be compromised. We will offer the behavior classes three times a day so that they can join according to their time availability. In addition, we will re-schedule the behavioral classes every other week based on their shift work. Third, we will collect the 24-h dietary recall on the days that are feasible to the participants. So, these may not be well representation of both week days and weekends. However, we will use the same strategy at all points of data collection. Therefore, the error will be non-differential to the cafeteria or behavioral intervention.

This pioneering study will investigate the effect of an environmental intervention to reduce cardio-metabolic risks and will estimate the added benefit of a proven individual-level dietary intervention for preventing cardio-metabolic risk. If the study demonstrates a significant effect, a scaled up approach could produce an important reduction in CVD burden through environmental and individual level prevention programs. The lessons learned may also be replicated in similar worksites in Nepal and translated to similar settings globally. The study needs to be tested in variety of workplace settings that are likely to represent different contexts that will be encountered at full scale. The study will provide the effectiveness of each level of intervention separately, which will be a vital information on what to focus in these settings in future. Advocacy, dialogue and planning with multiple stakeholders including the government and other partners would be necessary for scaling up the effective interventions at worksites to prevent cardio-metabolic risk. This study will provide the groundwork for it.

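### Only the behavioural arm is taught in classes of about 20, yet the test and power of the randomised comparison assume independent participants and leave almost no reserve for within-class correlation

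*Protocol article*

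**What the plan says.** All references are to the protocol article.

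- **Allocation** is individual (Step 2: The behavioral intervention): "half of the participants will be randomized using computer generated random numbers".
- **Delivery** is in groups, in CB only. The same section states "The behavioral intervention will be comprised of intensive education sessions, group counseling, and goal setting and monitoring exercises", in 24 one-hour sessions facilitated by a dietitian, and "There will be about 20 participants in each education class".
- **Contact within a class** is the stated exception to the no-sharing rule. Under Minimization of contamination, participants are told "not to provide any support to people in their worksite, other than their classmates".
- **Class times** are flexible for shift-working nurses (Discussion, limitations): "We will offer the behavior classes three times a day so that they can join according to their time availability". Classes are also rescheduled every other week.
- **Primary test** (Effectiveness of the behavioral intervention): the comparison is of those who "achieved two or more of their cardio-metabolic risk factor reduction goals in CO arm to the proportion of participants in the CB arm". The abstract names the method: "for the same outcome using a chi-square test".
- **Secondary tests** in the same section are a t-test on changes and, only if baseline differences appear, a GEE adjustment. The GEE cluster is not named.
- **Power** (Sample size and power): 320 participants, control risk 0.315, relative risk 1.5, "5% LTF rate with 80% power and 5% level of significance". No ICC or design effect is given. Table 3 gives detectable differences for 320 participants as independent samples.

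**The concern.** This is a partially nested design: individuals in CO, about 8 classes (160/20) in CB. People who share sessions, counselling and mutual support may have outcomes that resemble each other more than those of people in other classes. If so, the CB proportion is less precise than binomial variance implies. A chi-square test or ordinary t-test that ignores class then uses too small a standard error, and a sample size computed without a design effect is too small for a valid test.

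This comparison is the trial's only randomised one, and the article intends its results to inform scaling up.

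**Working it through.** **Inputs from the article.** CO risk 0.315; CB risk 0.315 × 1.5 = 0.4725; difference 0.1575; 320 randomised, 160 per arm, 152 per arm after 5% loss; class size about 20, hence about 19 analysed per class and 8 classes; alpha 5%, taken as two-sided.

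**Assumed.** ICC of 0.01, 0.02 or 0.05 (none is given), clustering in CB only, equal and stable classes.

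**Step 1: reproduce the plan's figures.** The usual two-proportion formula (pooled variance under the null, no continuity correction) gives 150 per arm, 300 in total, and 300/0.95 = 316 against 320 stated. Power at 152 per arm is 80.6%. For Table 3, (1.96 + 0.8416) × SD × √(2/152) gives:

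- HbA1c 0.122 (stated 0.12)
- diastolic pressure 3.03 (stated 3)
- systolic pressure 4.28 (stated 4.3)
- triglycerides 26.5 (stated 26.6)

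The agreement is close, and each calculation uses a design effect of 1.

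**Step 2: add class correlation in CB.**

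- Design effect: DE = 1 + 18 × ICC.
- Effective CB sample size: 152/DE.
- Standard error of the difference: SE = √[(0.315 × 0.685 + 0.4725 × 0.5275 × DE)/152].
- Power of a class-adjusted test: Φ(0.1575/SE − 1.96).
- Power of the planned chi-square: Φ[(0.1575 − 1.96 × SE₀)/SE], where SE₀ = √(2 × 0.39375 × 0.60625/152) is the pooled error that ignores class.
- Type I error of the planned test: 2 × [1 − Φ(1.96/√((1 + DE)/2))].

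| ICC | DE | Effective CB n | SE | Power, class-adjusted | Power, planned chi-square | Type I error, planned chi-square |
|---|---|---|---|---|---|---|
| 0 | 1.00 | 152 | 0.0553 | 81% | 81% | 5.0% |
| 0.01 | 1.18 | 129 | 0.0579 | 78% | 79% | 6.0% |
| 0.02 | 1.36 | 112 | 0.0604 | 74% | 78% | 7.1% |
| 0.05 | 1.90 | 80 | 0.0673 | 65% | 76% | 10.4% |

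Worked line for ICC 0.05: SE = √[(0.2158 + 0.2492 × 1.90)/152] = 0.0673; 0.1575/0.0673 = 2.34; Φ(2.34 − 1.96) = 65%.

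With a pooled null variance, class-adjusted power is 77%, 74% and 65%. A beta-binomial simulation (100,000 runs per ICC, 8 classes of 19 against 152 independent controls) gave type I error of 6.1%, 7.3% and 10.6%. These power figures use normal approximations and do not charge for estimating a class variance from about 8 classes.

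**Step 3: sample size for a class-adjusted test.** At 80% power with 5% loss, 1:1 allocation and 19 per class, the pooled formula gives 345, 374 and 461 in total for ICC 0.01, 0.02 and 0.05, against 316 at ICC 0.

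**Step 4: Table 3.** Detectable differences grow by √((1 + DE)/2) = 1.04, 1.09 and 1.20. For systolic pressure, 4.28 becomes 4.47, 4.65 and 5.15 mmHg.

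**The case against.** Several counterarguments carry weight.

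- **Size is assumed.** Without an ICC in the article, the magnitude cannot be fixed. At ICC 0 there is no problem, and at 0.01 to 0.02 it is modest. A common curriculum and an endpoint built on individual threshold crossings with large person-level variation (triglyceride SD 82.47 mg/dL against a goal of 10 mg/dL) point to the low end. This stands.
- **The null matters.** With individual allocation, if the classes influence nobody, the chi-square test keeps its level. Inflation requires class effects that are real but average to zero. At a risk of 0.315, ICC 0.05 means class success rates with an SD of √(0.05 × 0.2158) = 10 percentage points. This stands as a condition on the type I figures.
- **Classes may mix.** Flexible times and fortnightly rescheduling may weaken the correlation and make membership multiple. This complicates the model but does not make observations independent.
- **There may be spare numbers.** If all those remaining from 366 after 5% loss were randomised (366 × 0.95 ≈ 348, so about 165 analysed per arm), power would reach 80% at ICC 0.01 and about 77% at 0.02. The article, however, powers this step on 320.
- **A separate analysis plan could deal with class.** Possibly, but the article itself fixes the primary test and the power basis.

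Two stronger readings are not supported. A reader might infer that CB contributes only about 8 observations; that is true only at ICC 1, and the effective number over the range used here is about 129 to 80. A reader might also take 78% to 65% as the power of the planned chi-square; those figures belong to a valid class-adjusted test, while the planned test keeps about 79% to 76% at an inflated error rate.

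**Conclusion.** The point holds in a limited form. Group delivery in one arm is explicit, and the chi-square test, the between-arm t-test, the power statement and the independent-samples column of Table 3 make no allowance for it. The conditional GEE does not fill the gap, since it is secondary, depends on baseline imbalance and does not name class as the cluster.

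The article does not show that the error rate is in fact wrong, because that depends on an ICC it does not give. It does show that stated power has almost no reserve, so an appreciable positive ICC takes a valid analysis below the stated 80%. The likely consequence is modest at ICC 0.01 to 0.02 and material at 0.05, given stable classes of about 19 and, for the type I error, class effects without an average benefit. It should be put right before the randomised comparison is analysed.

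**What to change.** 1. Record a home class for each CB participant at randomisation, and the class actually attended at each session. Attendance is already to be measured under Intervention fidelity.
2. Make the CB against CO analysis partially nested, with class as the cluster in CB and CO participants as singletons. Use a mixed model, or GEE with class named as the cluster, with a small-sample correction for about 8 classes. Apply the same structure to the continuous outcomes.
3. Add a sensitivity analysis for mixed class membership.
4. State an assumed ICC range, for example 0.01 to 0.05, and restate the power (about 78% to 65% for 320 participants) and the independent-samples column of Table 3 (differences larger by a factor of 1.04 to 1.20).

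**Cost.** Class identifiers to record and a change of model; recruitment and the intervention are untouched. The interval will be somewhat wider, the class variance will be imprecisely estimated from so few classes, and the stated power will look less favourable.
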